### Statistical methods

#### Sample size calculation

According to the study of Kruizenga et al. [10], 412 patients per arm (a total of 824 patients for this study) are required to detect a difference in hospital stay of 2.6 days, assuming a standard deviation of 8 days in the intervention group and 13.3 days in the control group. Calculations were performed considering a two-tailed power of 90%, an alpha of 0.05, and 10% of potential losses.

#### Statistical analysis

Descriptive data analysis will present qualitative variables as frequencies and percentages, and continuous variables as means, medians, and standard deviations. Normality shall be verified by the Kolmogorov-Smirnov normality test. In bivariate analysis, depending on the nature of the variables, the parametric hypothesis test Student’s *t*-test or the non-parametric Mann-Whitney test will be used. To assess the effects of the intervention, changes in the primary and secondary outcomes will be analyzed by a between-group ANCOVA variance test. The analysis will control for the type, age, and sex of the patient, as well as the responsible medical unit. Patients admitted to Internal Medicine will be categorized into the four groups (1) cardiovascular, (2) neoplastic, (3) infectious, and (4) other patients, whereas patients in the Digestive and General Surgery services will be divided into the categories (1) neoplastic, (2) infectious, (3) obstructive, (4) inflammatory, and (5) others. The economic evaluation and statistical analyses of individual variables will be conducted in accordance with the intention-to-treat principle.

All tests will be two-sided with a type I error of 5%. Statistical analyses will be performed using the Statistical Package for Social Sciences (SPSS v.23, Chicago, IL, USA).

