### Endpoints

#### Primary endpoint

The primary endpoint of this study is the difference in mean length of hospital stay between the two compared groups. A difference of 2.6 days is considered clinically significant [13].

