#### Secondary endpoints

##### Mortality and morbidity

Rate of mortality in in-hospital patients.Rate of mortality in the course of three months post-discharge.Comorbidity will be assessed using the Charlson Index (CI) [14], which comprises 19 categories of the International Classification of Diseases, (10th revision) diagnose codes (ICD-10). It is based on a set of risk factors for the 1-year mortality risk and can be applied to establish the association between the life expectancy of a patient and the resources a health care system must allocate.

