##### Complications

Readmission rates, i.e., within 3 months post-discharge.Rate of surgical interventions during hospital stay.Incidence of clinical in-hospital complications according to the Classification of Hospital-Acquired Diagnoses (CHADx) [15]. The CHADx tool is a hierarchical classification of encoded diagnoses based on the International Classification of Diseases-10 (ICD-10), which allows quantification of the burden of in-hospital complications.Surgical complications according to the Clavien-Dindo classification, a standardized and internationally validated scoring system. The system allows for the severity of the complication and its interference in the clinical course of the operated patients. The highest grade complication (grades I-V) experienced by each patient was recorded [16].

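### One ANCOVA of changes is prescribed for every outcome, although most secondary outcomes are binary or ordinal and only EQ-5D-5L has a stated baseline

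*Protocol article*

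**What the plan says.** The Statistical analysis section introduces its method for the intervention effect in one sentence: "changes in the primary and secondary outcomes will be analyzed by a between-group ANCOVA variance test". The next sentence gives the covariates: "The analysis will control for the type, age, and sex of the patient, as well as the responsible medical unit". No baseline value of any outcome is among them. The only other between-group tests named are for bivariate analysis, where "the parametric hypothesis test Student’s *t*-test or the non-parametric Mann-Whitney test will be used", the choice depending on the kind of variable. No test or model for a binary outcome appears. Costs and QALYs have separate methods under Cost-effectiveness analysis.

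The primary endpoint is the "difference in mean length of hospital stay between the two compared groups". The secondary endpoints include:
- "Rate of mortality in in-hospital patients"
- "Rate of mortality in the course of three months post-discharge"
- "Readmission rates, i.e., within 3 months post-discharge"
- the rate of surgery during the stay, the incidence of CHADx complications and the rate of prescribed nutrition treatment
- surgical complications by Clavien-Dindo, for which "The highest grade complication (grades I-V) experienced by each patient was recorded"

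Measurement procedures states that EQ-5D-5L is collected at admission, at discharge and 3 months later. The Charlson Index, CHADx and Clavien-Dindo are documented after discharge.

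**The concern.** ANCOVA of a change needs two things: a roughly continuous outcome with similar residual variance across patients, and a baseline value of that outcome. Death, readmission, surgery and nutrition treatment are yes/no events. Clavien-Dindo is an ordered grade. None is measured before the intervention, so no change can be formed. Length of stay is also observed once.

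This is more than detail left to an analysis plan that is not shown. The article states a method and extends it to all outcomes, and a later plan could fit the endpoints only by departing from that sentence. At stake are the adjusted clinical secondary results: mortality, readmission and complications would be reported from a model not made for them, and Clavien-Dindo as a difference in mean codes.

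**Working it through.** **1. The plan's own figure.** The point concerns no stated number, but it uses the arm size, so that is checked first. Inputs (Sample size calculation): difference 2.6 days, SDs 8 and 13.3, two-sided alpha 0.05, power 90%, losses 10%.
- Mean variance = (8² + 13.3²)/2 = (64 + 176.89)/2 = 120.445, so SD = 10.975.
- n per arm = 2 × (1.960 + 1.282)² × 120.445 / 2.6² ≈ 374.4, rounded up to 375.
- With losses: 375/0.90 = 417, or 375 × 1.10 = 413.

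The stated 412 reproduces closely, and nothing below affects it.

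**2. Endpoints against the rule.** The items under the secondary endpoint headings, by scale and stated timing:

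| Heading | Items | Scale | Baseline and follow-up stated? |
|---|---|---|---|
| Mortality and morbidity | in-hospital death, 3-month death | binary | no |
| | Charlson Index | ordinal score | no |
| Complications | readmission, surgery, CHADx | binary (surgery and CHADx possibly counts) | no |
| | Clavien-Dindo | ordinal, I–V | no |
| Treatment | prescribed or not | binary | no |
| | time to treatment, characteristics | mixed | no |
| Quality of life | EQ-5D-5L | continuous index | yes |
| Biochemical, anthropometric, health care use | 3 items | mainly continuous | no |

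Binary: 2 + 3 + 1 = 6. Ordinal: 2. Together 8 of 14, and all 3 + 4 = 7 items under the first two headings. A change can be computed from the stated schedule for 1 of 14. The primary endpoint has no baseline either.

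**3. A plausible event rate.** The Background gives in-hospital mortality of 7.6% and 1.4% for CIPA-positive and CIPA-negative non-surgical patients, and 12.7% and 3.5% by one month after discharge. The Discussion gives 221 patients. The group sizes are not stated, but 79 and 142 is the only split of 221 that returns all four percentages: 6/79 = 7.6%, 2/142 = 1.4%, 10/79 = 12.7%, 5/142 = 3.5%. In-hospital mortality is then 8/221 = 3.6%, or 412 × 0.036 ≈ 15 deaths per arm. That this rate carries over to a trial that includes a surgical ward is an assumption.

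**4. What the linear model does to a binary outcome.**
- *Variance.* A yes/no outcome with probability p has variance p(1 − p). At 7.6% this is 0.076 × 0.924 = 0.0702, and at 1.4% it is 0.014 × 0.986 = 0.0138, a ratio of about 5. Constant variance across patients does not hold.
- *Arm effect.* The arm coefficient is an adjusted difference in proportions, that is, a risk difference. In simulated trials of 824 patients with equal arms, no true arm effect, and arm, age, sex and the nine diagnosis categories (4 medical + 5 surgical) in the model, the arm test rejected in about 4–6% at a nominal 5%. Bias was about 0.1 percentage point or less.
- *Fitted values.* At a 3.6% event rate, about 4–21% of patients received a negative fitted probability. The range runs from no covariate effect to strong effects, all assumed, since the documents give none. This shows poor fit for individual patients; it does not show error in the arm comparison.

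**5. Clavien-Dindo.** A mean of the codes 1 to 5 makes each one-grade step count the same. The Complications section presents the scale as a ranking of severity and gives no ground for equal spacing.

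**The case against.** The case against has several parts that stand. *Changes* may be loose wording for differences between arms: the sentence is about intervention effects and a between-group test, and the primary endpoint is itself defined as a difference between groups. On that reading the missing-baseline part falls away. Bivariate tests are chosen by the nature of the variable, and Mann-Whitney gives an unadjusted route for grades and skewed counts. CHADx is described by incidence, so it need not be a count. A choice between, say, penalised and ordinary logistic regression belongs in an analysis plan.

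A reader might go further and infer that the mortality and readmission comparisons would be biased or produce false positives, or that negative fitted probabilities invalidate them. The documents do not support this. The analysis plans no individual prediction, the arm coefficient is an interpretable risk difference, and the simulated error rate stayed near 5%.

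What the objection does not remove is the adjusted effect analysis. On either reading of *changes*, the plan fits a constant-variance linear model to rates and averages ordinal codes. The simulations covered binary outcomes only and do not defend the treatment of Clavien-Dindo.

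**Conclusion.** The point holds as a mismatch between a stated rule and the endpoints it governs. Eight of 14 secondary items are binary or ordinal, and one of 14 has a stated baseline and follow-up. If *changes* is meant literally, it is undefined for nearly all outcomes, including length of stay. If it means differences between arms, the linear model is still ill-suited to the rates and unsuitable for the Clavien-Dindo grade.

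The size of the harm is modest. For binary outcomes, neither bias nor type I error inflation has been shown at 412 per arm. That conclusion rests on the assumed event rate and covariate effects and on equal arms. The primary comparison of mean stay, the sample size and the cost-effectiveness methods are not undermined. The sentence should be corrected before analysis, but it does not threaten the trial's main result.

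**What to change.** Replace the single ANCOVA sentence with a rule by outcome type, keeping the covariates already listed:
- *Length of stay:* adjusted difference in means, with no reference to change.
- *Binary outcomes* (both mortality outcomes, readmission, surgery, any CHADx complication, prescribed nutrition treatment): logistic regression, reporting the marginal risk difference and risk ratio with 95% confidence intervals.
- *Clavien-Dindo grade:* ordinal regression.
- *CHADx:* a count model only if the number of complications is what will be analysed; state which.
- *EQ-5D-5L:* ANCOVA of the follow-up scores with the admission score as covariate.

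Delete the reference to changes for every outcome without a baseline.

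The cost is a few lines of text and no new data. The models exist in standard software, and the marginal risk measures need at most one extra step after the logistic fit. The article says that data are still being collected and that analysis comes after follow-up, so the change can be recorded before results are seen.

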#### Cost-effectiveness analysis

We will analyze the cost and cost-effectiveness of implementing the malnutrition screening tool CIPA versus standard practice in patients admitted to the Internal Medicine and General and Digestive Surgery wards. These analyses will be in line with accepted economic evaluation methods.

The cost will be assessed from a National Health Service perspective and, therefore, only include medical costs incurred by the health care service. Based on data from the hospital as well as the national sources, we will assign a unit cost to each component of health care utilization collected in this trial.

The cost-effectiveness measure will be the incremental cost per quality-adjusted life year (QALY) gained. QALYs will be calculated based on the HRQoL and mortality data collected during the trial. Patient-specific utility profiles will be created assuming a straight-line relation between all patients’ EQ-5D-5 L scores from either follow-up point. The QALYs experienced by each patient from baseline to 3 months will be calculated as the area underneath this profile. We will investigate differences in baseline characteristics and, if necessary, use regression methods to control for them.

Cost-effectiveness will be summarized as the incremental cost-effectiveness ratio (ICER) by dividing the estimated differences in cost by the differences in QALYs. Non-parametric methods to calculate confidence intervals around the ICER, based on bootstrapped estimates of the mean cost and QALY differences, will be used. Further, the bootstrap replications will be used to create a cost-effectiveness acceptability curve, which will reveal the probability that each alternative is cost effective for different values of willingness to pay for an additional QALY. We will also subject the results to extensive, deterministic (one, two-, and multi-way) sensitivity analyses.

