##### Health care utilization

Health care utilization includes staff time and material required to implement the malnutrition screening tool CIPA, duration of tube feeding or any other nutritional treatment, visits from other specialists during hospitalization, in-hospital complications, hospital length of stay, and readmissions and other health care contacts within 3 months after discharge.

In addition, the following patient information was collected upon admission: initials, the assigned ward, clinical record, nationality, age, sex, type of admission (emergency or scheduled), date of and diagnosis on admission. Subsequently, the diagnosis-related group (DRG) as well as the severity-based DRG were established.

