### Measurement procedures

Data collection is being managed using an electronic case report form (CRF), designed for this study and complemented with EMR information and patient questionnaires conducted by phone 3 months past discharge.

The project data manager compiles all clinical data from the EMR, except for the EQ-5D-5 L questionnaires, which are being collected at hospital admission, discharge, and 3 months post-discharge, and the DRG and severity-based DRG, which are presented by the Management Unit following hospital discharge. The main data and laboratory parameters of included patients are directly recorded in the CRF. The CI and the CHADx and Clavien-Dindo classifications are documented by the medical staff subsequent to the patient’s discharge.

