#### Duration of fieldwork

The recruitment phase lasted for 15 months. Patients are being followed up for three more months post-discharge. Thereafter, a subsequent phase of data cleansing, identification of unit costs, and data analyses will take place.

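### The QALY window ends 3 months after discharge, so it lengthens with hospital stay and credits the longer-stay arm with extra QALYs

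*Protocol article*

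**What the plan says.** The Cost-effectiveness analysis section builds the QALY in two steps. First, "Patient-specific utility profiles will be created assuming a straight-line relation" between the EQ-5D-5L scores. Then, "The QALYs experienced by each patient from baseline to 3 months will be calculated as the area underneath this profile." The QALY difference between arms is the denominator of the ICER.

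The Measurement procedures section gives the times of those scores, "which are being collected at hospital admission, discharge, and 3 months post-discharge." No questionnaire is scheduled at 3 months from admission.

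The article's other 3-month periods start at discharge. Duration of fieldwork says "Patients are being followed up for three more months post-discharge." Health care utilization counts "hospital length of stay, and readmissions and other health care contacts within 3 months after discharge." Mortality and morbidity lists "Rate of mortality in the course of three months post-discharge," and the readmission endpoint under Complications uses the same anchor.

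Under Primary endpoint, the outcome is the difference in mean length of stay, and "A difference of 2.6 days is considered clinically significant."

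**The concern.** A QALY comparison needs the same span of time for every patient. If the area is taken under the whole profile, its width is the patient's own stay plus 3 months. Two patients with identical scores at all three assessments then get different QALYs, and the one who stayed longer gets more. The shorter-stay patient is also alive on the days just after the window closes, but those days are not counted.

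The width of the window is set by an outcome measured after allocation, so randomization does not balance it. The planned regression adjustment concerns baseline differences and cannot remove it. The bootstrap resamples the same shifted difference. The sensitivity analyses are described only in general terms and do not mention the horizon.

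At stake is the QALY difference in the ICER and the acceptability curve. It is likely to be small, so a small artefact matters. The artefact works against CIPA if CIPA does shorten stay.

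**Working it through.** **Inputs from the article.** Target difference in stay 2.6 days (Primary endpoint; Sample size calculation). Scores at admission, discharge and 3 months after discharge, joined by straight lines. The 12.63-day stay used below is the mean for CIPA-negative patients in the Background; it serves only as an illustration.

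**Assumptions.** The article gives no utility values, so ranges are shown. Three months is taken as 91.3 days and a year as 365.25 days. The 2.6 days are taken to fall on patients who survive to the last assessment.

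**The plan's own figure.** The article gives no QALY figure. The 2.6 days is the difference it was sized on: (8² + 13.3²) × (1.960 + 1.282)² / 2.6² = 374.4 per arm, and 374.4 × 1.1 = 411.9, which is the stated 412.

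**Step 1: which part of the area changes.** For stay L (days) and utilities u0, u1, u2 at the three assessments,

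QALY = [L × (u0 + u1)/2 + 91.3 × (u1 + u2)/2] / 365.25.

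The second term is the same whatever the stay. With identical utilities in both arms, a stay longer by 2.6 days therefore adds 2.6/365.25 × (u0 + u1)/2, that is, 2.6/365.25 times mean in-hospital utility.

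| Mean in-hospital utility (assumed) | Extra QALY in the longer-stay arm |
|---|---|
| 0.3 | 0.0021 |
| 0.5 | 0.0036 |
| 0.6 | 0.0043 |
| 0.8 | 0.0057 |

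The longer arm's window is wider by 2.6/91.3 = 2.8% of 3 months. If utility is constant over time, a fixed window gives a difference of exactly 0.

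**Step 2: a recovering patient.** Utilities 0.4, 0.6 and 0.7 in both arms; stays 12.63 days (intervention) and 12.63 + 2.6 = 15.23 days (control).

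- Stay plus 91.3 days: intervention (12.63 × 0.5 + 91.3 × 0.65)/365.25 = 65.66/365.25; control (15.23 × 0.5 + 91.3 × 0.65)/365.25 = 66.96/365.25. Control minus intervention = 1.30/365.25 = **+0.0036**.
- Fixed 91.3 days from admission: utility at day 91.3 is 0.6 + 0.1 × 78.67/91.3 = 0.6862 (intervention) and 0.6 + 0.1 × 76.07/91.3 = 0.6833 (control). The areas are 6.315 + 78.67 × 0.6431 = 56.91 and 7.615 + 76.07 × 0.6417 = 56.43 utility-days. Control minus intervention = −0.48/365.25 = **−0.0013**.

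The same patients give opposite signs. The fixed window favours the arm that reaches its discharge utility sooner; the discharge-anchored window favours the arm that is counted for longer.

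**Step 3: scale.** A utility gain of 0.02 held for 91.3 days (an assumed benchmark) is 0.02 × 91.3/365.25 = 0.0050 QALY. The artefact reaches that size only when mean in-hospital utility exceeds 0.0050/(2.6/365.25) = 0.70. The sustained gain that CIPA would need merely to break even is 2.6 × u/91.3: 0.011 at u = 0.4, 0.017 at 0.6 and 0.023 at 0.8.

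**The case against.** The strongest reply is that the Cost-effectiveness analysis section already fixes the horizon. Read literally, baseline to 3 months is one common period from admission, and a straight-line profile can be cut there by interpolation. An article may also leave such detail to the full protocol. This reply stands in part: the wording permits that reading, so the bias is not certain. But no score is taken at that time, no cut is described, and the article's other 3-month periods start at discharge. The more natural reading is the area under the whole profile.

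A reader might infer that costs are distorted in the same way. The documents do not support that. The post-discharge part, "readmissions and other health care contacts within 3 months after discharge," has the same length for all survivors, and the extra inpatient cost of a longer stay is a real effect that belongs in the total.

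A reader might also infer that the mortality and readmission endpoints are wrongly defined. They are not. In-hospital death and death after discharge are separate, legitimate secondary endpoints. Cutting readmissions at a fixed day from admission would give longer-stay patients fewer days at risk after discharge, which creates the opposite imbalance.

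Finally, a reader might infer that the artefact would wipe out a plausible benefit. Only in-hospital utility enters it, probably the patient's lowest period, and the EQ-5D index can even be negative. At 0.5 or 0.6 the artefact is smaller than the 0.0050 benchmark, the benchmark itself has no source in the article, and the full 2.6-day effect is assumed.

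**Conclusion.** The point holds for QALYs. As most naturally read, the plan counts QALYs over the stay plus 3 months and so ties the window to the primary outcome. At a 2.6-day difference, and for assumed mean in-hospital utilities of 0.3 to 0.8, the longer-stay arm gains about 0.0021 to 0.0057 QALY per patient from window length alone. If CIPA shortens stay, the ICER denominator is biased against it, and with recovering utilities the sign of the QALY difference can depend on the window chosen (+0.0036 against −0.0013 for control in the illustration). If the literal fixed-window reading was meant, there is no bias, but the text still has to state the anchor and the cut.

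The result rests on positive in-hospital utility, on the target difference occurring, and on utility values that the article does not supply. It does not extend to a claim of bias in the cost, mortality or readmission definitions. Length of stay as primary endpoint and the sample size are untouched. This should be settled before the economic analysis is run.

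**What to change.** In the Cost-effectiveness analysis section, fix one QALY horizon from admission for every patient, for example day 90. Interpolate the straight-line profile to that day from the scores already collected, with utility 0 from the date of death. Count the costs that enter the ICER over the same horizon where the dates of resource use allow; the article does not say whether post-discharge contacts are dated, so this needs checking. Report the stay plus 3 months version as a sensitivity analysis.

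Leave the in-hospital and post-discharge mortality and the readmission endpoints as defined. All-cause death by day 90 from admission in the analysed patients can be added if dates of death are recorded.

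The QALY change needs wording and a cut by date, with no new questionnaire: for almost every survivor, day 90 from admission falls before the last assessment. The cost is that utility and costs after day 90 leave the main economic analysis, and that utility at day 90 is interpolated rather than measured.

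### Baseline EQ-5D should be a fixed covariate in the QALY analysis; adjusting only if it seems necessary makes the estimator data-dependent and gives up precision

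*Protocol article*

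**What the plan says.** - **Cost-effectiveness analysis.** QALYs are the area under each patient's EQ-5D-5L profile from baseline to 3 months. On baseline adjustment the article says: "We will investigate differences in baseline characteristics and, if necessary, use regression methods to control for them". No trigger and no covariates are given.
- **Measurement procedures.** EQ-5D-5L is collected at admission, at discharge and 3 months after discharge, so a baseline value is planned for every patient.
- **Statistical analysis.** For effects of the intervention, "changes in the primary and secondary outcomes will be analyzed by a between-group ANCOVA variance test". The covariates are fixed: "The analysis will control for the type, age, and sex of the patient, as well as the responsible medical unit". Baseline EQ-5D is not among them. Patient type is not defined, but the next sentence goes straight to diagnosis: "Patients admitted to Internal Medicine will be categorized into the four groups", followed by five surgical groups.
- **Health care utilization.** Emergency or scheduled admission is recorded on admission.
- **Mortality and morbidity**, under Secondary endpoints: "Comorbidity will be assessed using the Charlson Index". Measurement procedures adds that staff document the index after discharge.

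**The concern.** Baseline utility enters the QALY twice: directly, as the first point of the area, and indirectly, because patients with better scores at admission tend to have better scores later. It therefore belongs in the model whatever imbalance is observed. A rule that first looks at baseline differences and then decides has two costs. The estimator, and the interval that goes with it, depend on a step that the article does not describe and that a reader could not reproduce. And much of the available precision is lost, because adjustment reduces variance over the whole range of chance imbalance and not only when the imbalance looks large.

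This matters because the QALY difference is the denominator of the ICER and accrues over little more than three months. The acceptability curve is built from the same bootstrap replicates, so the choice of estimator carries straight into it.

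**Working it through.** **The plan's own figure.** Sample size calculation says that "412 patients per arm (a total of 824 patients for this study) are required to detect a difference in hospital stay of 2.6 days". Its other inputs are SDs of 8 days (intervention) and 13.3 days (control), two-sided alpha 0.05, power 90% and a 10% allowance for losses.

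n = (8² + 13.3²)(1.960 + 1.2816)² / 2.6² = 240.89 × 10.51 / 6.76 = 374.4 per arm. Then 374.4 × 1.10 = 411.9, so 412 is reproduced. This point does not affect it. After 10% losses, 412 × 0.9 ≈ 371 per arm are evaluable, and power for length of stay is 89.7%.

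**QALY weights.** Assume a common stay of ℓ = 15/365 = 0.0411 year (the earlier CIPA study in Background had means of 12.63 and 19.53 days), then 0.25 year to follow-up. The straight-line area is

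Q = (ℓ/2)(u0 + u1) + (0.25/2)(u1 + u2) = 0.0205·u0 + 0.1455·u1 + 0.125·u2.

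**Share of QALY variance explained by baseline.** Assume equal variances σ² and a common correlation ρ between time points.

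- cov(u0, Q)/σ² = 0.0205 + 0.2705ρ
- var(Q)/σ² = 0.0372 + 0.0475ρ
- R² = cov² / (σ² · var Q), in which σ cancels

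| ρ | cov/σ² | var/σ² | R² | Always adjust: 1 − R² |
|---|---|---|---|---|
| 0.3 | 0.102 | 0.0515 | 0.20 | 0.80 |
| 0.5 | 0.156 | 0.0610 | 0.40 | 0.60 |
| 0.7 | 0.210 | 0.0705 | 0.63 | 0.37 |

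**Adjustment only if the baseline difference has p < 0.05** (one possible reading of the clause). The part of the gain kept is 1 − E[Z²; |Z| < 1.96] = 1 − (0.95 − 2 × 1.96 × 0.05845) = 0.28. Relative variance is then 1 − 0.28R² = 0.94, 0.89 and 0.83.

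**Simulation check** (371 per arm, utility SD 0.3, 4,000 replicates). Variance relative to no adjustment:

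| ρ | Always | Only if p < 0.05 | Ratio, always to conditional |
|---|---|---|---|
| 0.3 | 0.80 | 0.92 | 0.87 |
| 0.5 | 0.60 | 0.88 | 0.68 |
| 0.7 | 0.36 | 0.81 | 0.44 |

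The two routes agree to within about 0.02, which is simulation error. The standard error of the QALY difference is 0.0047 to 0.0053 under the conditional rule and 0.0035 to 0.0044 with fixed adjustment.

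**What a chance imbalance can do.** The edge of the 95% chance range for the baseline gap is 1.96 × SD × √(2/371) = 0.029 for SD 0.2 and 0.043 for SD 0.3. Multiplied by the covariance weight above, for stays of 12.63 to 19.53 days and ρ of 0.3 to 0.7, this moves an unadjusted QALY difference by about 0.003 to 0.010.

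**Further covariates for length of stay.** With residual SD = 10.97 × √(1 − R²) and 371 per arm, assumed added R² of 0.02, 0.05, 0.10 and 0.20 gives power of 90.3%, 91.2%, 92.5% and 95.0%. The 95% half-width falls from 1.58 days to 1.56, 1.54, 1.50 and 1.41.

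**The case against.** The strongest reply is that the article does provide for regression, sets no significance threshold, and may leave the details to an analysis plan that is not shown. The analysts could adjust for any gap they think matters. Most of this stands. The p < 0.05 rule is only one reading, so the conditional figures illustrate the cost and do not describe the stated plan. What does not fall away is that the article states a rule, and the rule makes adjustment depend on the observed data for a variable that forms part of the outcome.

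Several stronger readings are tempting, and the documents do not support them:

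- **Chance imbalance is left uncorrected, or the result is biased.** Correction is allowed for, and age, sex, patient type and unit are already fixed for the clinical outcomes. Under sound randomisation, chance imbalance costs precision and does not bias the estimator.
- **The trial forgoes the whole gain from adjustment.** That compares always adjusting with never adjusting, and never adjusting is not the plan.
- **Changes in EQ-5D are unadjusted for baseline.** An ANCOVA of changes may well carry the baseline value. The article does not say.
- **Admission type is ignored.** Patient type probably means diagnostic group, but it is undefined, so the omission is likely and not certain.
- **The Charlson index will be tested as an outcome.** The block headed Secondary endpoints also holds age, sex, nationality and anthropometry. It works partly as a list of collected variables, so the placement alone proves nothing.
- **The Charlson index is a covariate without risk.** It is documented after discharge, and Blinding says the research team knows the group. Unless limited to conditions present on admission, it could carry post-randomisation information.

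**Conclusion.** The point holds as one of precision and pre-specification in the QALY analysis. Under the assumed inputs, fixed adjustment for baseline EQ-5D cuts the variance of the QALY difference by about 20% to 64%. A significance-triggered rule would keep only about 30% to 40% of that reduction in the simulation (28% in the closed form). Utility SD, correlations and the common stay are assumptions, and the model takes complete data with equal correlations. Deaths, missing questionnaires and variable stays would change the figures, but not the direction as long as baseline utility predicts later utility.

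The primary endpoint and sample size are unaffected. For length of stay the gain from further covariates is probably modest and rests on an R² that the documents do not give. The documents state no expected QALY difference, so they do not show that baseline imbalance would decide its sign.

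**What to change.** 1. In Cost-effectiveness analysis, delete the conditional clause. State that QALYs are always adjusted for the baseline EQ-5D index together with the covariates in Statistical analysis, with the regression refitted within each bootstrap replicate.
2. In Statistical analysis, name the baseline EQ-5D index as a covariate for follow-up EQ-5D.
3. Define patient type. If it means diagnostic category, add emergency or scheduled admission as a covariate for length of stay and costs.
4. List the Charlson index as a baseline characteristic and not as an endpoint. Use it as a covariate only if the recorded data allow restriction to conditions present on admission.

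Items 1 to 3 change wording only and use data already being collected, for a few degrees of freedom. Item 4 needs a check of how the index was coded before it enters any model. All should be settled before the analysis starts; Trial status says data were still being collected.
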